**Figure 1 F1:**
[figure not shown]
Study design

## Procedures

### Enrolment

A 15-month period is expected for enrolment of study participants. Screening of participants will consist in the evaluation of inclusion and exclusion criteria, explanation of the study protocol, and the assessment of the willingness to participate in the study, (Figure 1). Eligible subjects will be scheduled to the following visits:

**- Visit A**: consists of a structured validated interview (socio-demographic data, habits, and medical record) and a detailed physical examination by a nurse and a gynecologist. Prenatal care visits will be continued in the primary care center assigned to the healthcare insurance plan of each woman.

### Baseline assessments and active follow-up

**- Visit B**: measurements of blood pressure, anthropometric parameters, FMD, functional capacity (VO_2Max_), and electrocardiogram. During this visit, the participants will be randomized to one of the four intervention groups. For this purpose, a randomization system using maximum blocks of 10 will be used.

**- Visit C**: within 32 and 36 week period of gestation, measurements described above are repeated.

**- Visit D**: the following pregnancy outcomes will be recorded at postpartum: pregnancy duration, blood pressure, characteristics of delivery (route and duration of delivery, and postpartum haemorrhage), newborn outcomes (gestational age at birth, Apgar score, weight, height, head circumference, and abdominal circumference). With these measures, the following variables will be calculated: weight/height^3^, head circumference/birth weight, and weight/height [27]. In umbilical cord blood, measurements of the following outcomes will be obtained: oxidative stress biomarker (F_2_-isoprostanes). In addition, the number of prenatal controls and information regarding pregnancy complications will be registered.

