#### 2. Exercise Group

Regular aerobic exercise: walking (10 minutes), aerobic exercise (30 minutes), stretching (10 minutes), and relaxation exercises (10 minutes) during a three-month period. Exercise will be performed during 3 sessions per week. A physical therapist and a physical educator will supervise all sessions. The exercise-program is according to the American College of Obstetrics and Gynecology (ACOG) [18] and the American College of Sports Medicine (ACSM) exercise prescription [19]. Aerobic activities will be performed at moderate intensity (60-70% of maximal heart rate) measured by the 6-20 Borg's rating scale (PER). Each session will start with a 5 min warm up, followed by 30 min of aerobic activity, including a 5 min cool down. Subsequently, a 15 min strength training for upper limbs, lower limbs, and deep abdominal muscle stabilization. The last 5 min consist of stretching and relaxation exercises. (Table 1)

**Table 1 T1:** Pregnancy 2 X 2 Factorial Design

	Regular Physical Exercise	
	
	-	+

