### Sample size

Measurement of endothelial function (FMD), validated in several population studies was selected as the critical variable to calculate the sample size. Sample size was conservatively calculated to detect all six pairwise difference between treatment groups with a Bonferroni adjustment for an overall 0.05 type I error (0.05/6 = 0.0083) [20]. A sample size of 320 subjects or 80 per treatment group was estimated. The sample size was calculated assuming a specific difference between the groups of 4.3% in the FMD after 3 months of treatment with 11 of maximum standard deviation. It was accepted a type I error of 0.05, a power of 80%, and it was adjusted by 20% [20].

Eligible women for the present study and those interested in participating will be invited to a pre-test that includes an interview (Visit A) and further assessments that will be performed at the Red de Salud Ladera (Hospital Cañaveralejo, Centro de Salud Meléndez, Centro de Salud Siloé, Hospital Universitario del Valle) and at the Laboratory of Biochemistry of the Universidad of Valle, Cali-Colombia. The first visit will take place between weeks 12 and 20 (Visit B), the second at week 32 and 36 (Visit C) and the last one, after delivery (Visit D).

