### Settings

The trial will be conducted in Cali, the third largest city of Colombia. The study will be carried out in six public health care institutions, which offer prenatal care in the first level of complexity to people living in the lowest socioeconomic stratum of the population. These institutions are located in the southwest area from Cali (*Red de Salud Ladera*) and provide services mainly for the government-subsidized population in the Colombian healthcare system. The Ethics Committees of Universidad del Valle and Red de Salud Ladera (Resolution-017/08-UV and SCAH/0408-A/08) approved the trial. All participants will provide written informed consent before entering the study.

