In order to evaluate the effects of maternal regular physical exercise and micronutrients supplementation on newborn's oxidative stress (concentration of F_2_-Isoprostanes in umbilical cord blood), a comparative analysis will be executed to establish if the effects are different among study groups using analysis of covariance (ANCOVA), a form of general linear model [26]. We will include the baseline measure as a covariate in the model and pre-specified potential confounding factors: maternal age, previous physical exercise level, tobacco or alcohol consumption, differences in diet report and pregnancy complications such as hypertension and diabetes [26]. These will be included regardless of whether baseline imbalance exists. This approach has been chosen because confounder selection strategies that are based on collected data can result in models with poor statistical properties [26]. This will adjust appropriately for any baseline imbalance and will provide the most powerful analysis. Adjusted estimates of intervention effect from this model will be reported as the primary analysis in the trial publication.

Finally, we will investigate if there is an interaction between the two interventions for the primary outcome at 32 gestational weeks (regular physical exercise) or until the birth (micronutrients supplementation). For these analyses we will include appropriate interaction terms in the models [26]. The trial is not powered to detect these interactions and is likely to have poor precision for the interaction terms. We plan to report regression coefficients for the interaction terms and their 95% confidence intervals.

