### Blinding and Randomization methods

The randomization procedure into the two study arms was performed by the Fundación FES Social, Division de Salud, Cali-Colombia (Biometry and Epidemiology Department). The biometricians compiled an allocation list which was the basis for the pharmacists to prepare sequentially numbered envelopes containing two boxes of study medication for trial use. The boxes contained a zinc (30 mg), selenium (70 μg), vitamin A (400 μg), alphatocopherol (30 mg), vitamin C (200 mg), and niacin (100 mg) or an equivalent placebo capsule (maltodextrine). After inclusion into the trial, the study researcher assigned the content of the lowest numbered envelope to the participant. The principal investigator and coordinator the allocation sequence, and randomization is performed through a secure website which ensures allocation concealment. All participants and study personnel (including investigators, research coordinators, data analysts) will be blinded to treatment allocation throughout the trial (Table 1). Access to the allocation code will be restricted to one study statistician who will not perform the final study analyses. Also, neither the participant nor the study researcher knew about the content of the boxes, the capsule was not distinguishable. Since no specific qualifications or experience are required for the research assistants, training will be provided prior to the initiation of the trial about protocol and measurement procedures and methods used to maintain the blindness. These procedures are also detailed in the study operations manual. Moreover, the importance of maintaining the blinding and allocation concealment will be reinforced by regularly scheduled conference calls at the sites and daily meetings with the field investigators, Figure 1.

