## Study conduct and monitoring

The study will be conducted according to Good Clinical Practice and to standard operating procedures. The Human Ethical Committee at the Universidad del Valle will monitor this clinical trial. The coordinating center will be composed by physical educators, physicians, gynaecologists, nurses, physical therapists, clinical epidemiologists, and bacteriologists. Preliminary monitoring reports will be submitted to the experts, focusing on patient intake, adherence to protocol, baseline comparability of treatment groups, completeness of data retrieval, and adverse events. All adverse events will also be reported to the Ethics Committee of the Universidad del Valle. To standardize study procedures, an operations manual has been written and comprehensive training sessions will be held prior to the initiation of the trial. In addition, there will be weekly conference calls between the sites, the coordinating center, and the research chief in order to review procedures and address problems. To ensure the uniformity and quality of the interventions at each site, experts in exercise physiology will train all the therapists prior to the trial initiation and consult with them on an ongoing basis. The coordinating center will supervise the procedures to ensure the quality and integrity of the data. These processes that include inspections of the data forms as they are received from locations and periodic reviews of the computer data files will be performed in order to identify out of range values and missing data forms.

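### The covariate list fixed in advance for the adjusted analysis omits institution in a six-institution trial, which costs a little precision but causes no bias

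*Protocol article*

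**What the plan says.** Settings: "The study will be carried out in six public health care institutions". Under the exercise group, "A physical therapist and a physical educator will supervise all sessions". Study conduct and monitoring treats differences between sites as something to be managed: "To ensure the uniformity and quality of the interventions at each site, experts in exercise physiology will train all the therapists".

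On allocation, Blinding and Randomization methods says that "The biometricians compiled an allocation list which was the basis for the pharmacists to prepare sequentially numbered envelopes", and that each new participant receives the lowest-numbered envelope. The Visit B text adds only "For this purpose, a randomization system using maximum blocks of 10 will be used". Neither place mentions institution, either as a stratum or as something left out on purpose.

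On analysis, the Analytic plan gives the F2-isoprostane ANCOVA a baseline measure and "pre-specified potential confounding factors: maternal age, previous physical exercise level, tobacco or alcohol consumption", followed by reported diet and pregnancy complications. These enter regardless of imbalance. Choosing confounders from the collected data is rejected, the model is described as the most powerful available, and its adjusted estimates are to be the primary analysis in the publication. For FMD the plan names one-way ANOVA or Kruskal-Wallis and then GEE. It gives no institution term there.

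**The concern.** Institution is known before randomisation, costs nothing to record, and plausibly relates to the outcomes through image acquisition, the way sessions run, local prenatal care and cord-blood sampling. The plan manages these differences operationally but leaves them out of the model.

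This is more than a detail left for later. The covariate list is named and closed, and the plan's own argument against data-driven selection means that institution could not properly be added after the data are seen. The claim to the most powerful analysis also sits awkwardly with leaving out a design factor. At stake is the precision of the treatment effects, not their validity.

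**Working it through.** **Inputs from the article.** 320 women, 80 per group, so 160 v 160 for the exercise main effect; FMD difference 4.3; SD 11; six institutions. The article gives no figure for variation between sites. The 80 per group does not follow from its own inputs: 2 × (2.638 + 0.842)² × (11/4.3)² = 159 per group at two-sided 0.0083, before the 20% adjustment. That is a separate matter, and 320 is taken as given here.

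**Assumptions.** Institution explains a share ρ = 0.01, 0.05 or 0.10 of outcome variance; six sites recruit with equal probability; blocks of 4 and 8.

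**Reference standard error.** 11 × √(2/160) = 1.230.

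**Simulation of the exercise effect (3,000 runs per setting), one central sequence.**

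| ρ | SE without institution | SE with institution | Ratio | Equivalent women, 320 × [(SE without / SE with)² − 1] |
|---|---|---|---|---|
| 0.01 | 1.222 | 1.220 | 0.998 | 1 |
| 0.05 | 1.216 | 1.191 | 0.979 | 14 |
| 0.10 | 1.229 | 1.183 | 0.963 | 25 |

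**Closed-form check.** With six sites, 5/6 of the between-site variance is expected to appear within the trial, and fitting five institution terms costs a factor √[1/(1 − 5/319)] = 1.008. The expected ratio is √[(1 − ρ)/(1 − ρ + 5ρ/6)] × 1.008.
- ρ = 0.01: 0.996 × 1.008 = 1.004
- ρ = 0.05: 0.979 × 1.008 = 0.987
- ρ = 0.10: 0.957 × 1.008 = 0.964

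The gain is therefore nil at 1%, between 1% and 2% at 5%, and just under 4% at 10%. The two methods differ by simulation error.

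**Power.** If all of the institution variance were removed, the SD would become 11 × √(1 − ρ). Main-effect power at two-sided 0.05 would rise from 93.8% to at most 95.8% (ρ = 0.10). Pairwise power at 80 v 80 and two-sided 0.0083 would rise from 43.4% to at most 48.7%.

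**Does stratified allocation add anything?** At ρ = 0.10, blocking within institution with institution in the model gives an SE of 1.186, against 1.183 for a central sequence with the same model. The two are equal within simulation error. Blocking does even out numbers: the mean worst-site departure from a 50:50 exercise split falls from about 10 to about 2 percentage points.

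**The case against.** The case against has several sound parts.

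- **Allocation.** A reader might infer that allocation is not blocked by site. The wording does read like one list, but nothing in the article says so, and a condensed article commonly leaves stratification factors to the full protocol. All that can be said is that no site stratification is described.
- **Bias.** A reader might take uneven site numbers as a threat to validity. Under randomisation, chance imbalance adds noise and no bias.
- **Size.** A shortcut such as 320/0.95 − 320 = 17 or 320/0.90 − 320 = 36 women suggests more. It treats the whole assumed share as removable and ignores the cost of fitting the terms. The simulated figures are 14 and 25, and about 1 if the share is 1%.
- **FMD.** The outcome is change from baseline, and recorded images are read by two blinded observers whose values are averaged. This removes much of any stable site or reader difference. It does not remove site differences in acquisition that drift over time, or in session delivery.
- **Cord blood.** The article describes one assay method and places its biochemical processing in one university laboratory. Site variation can enter only through delivery and sampling, but no earlier cord value exists to absorb it.
- **Therapists.** It is tempting to say that therapist differences add noise to both factors. They exist only in the exercise arms, and neither site blocking nor a site fixed effect removes them.
- **Number of sites.** Six institutions for the trial and four facilities named for assessments can both be true, so this is not a contradiction.

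It can also be said that the named list belongs to the F2-isoprostane model and contains confounders, so that a site term is only a preference. That stands in part: the FMD model has no closed list. It does not rescue the F2-isoprostane model, whose list is fixed and whose estimates are called primary.

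**Conclusion.** The point holds as a modest loss of precision. The covariate list for the analysis to be reported as primary omits institution, and no institution term is named for FMD. If institution explains 1-10% of variance, the avoidable cost is roughly 0-4% in the standard error, with no bias. This rests on the assumed shares, on equal recruitment across six sites, and on a simulation that used the FMD standard deviation. The relative loss carries over to F2-isoprostanes only if their site share is similar. That outcome has the stronger case for the term, because no pre-treatment cord value is available. The documents do not support a claim that allocation ignores site, that the treatment effects are biased, or that the site counts conflict. The change is worth making because it is nearly free and must be made before the data are seen.

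**What to change.** 1. Add institution as a fixed effect to the pre-specified covariates of both the FMD and the F2-isoprostane models. If the GEE models both visits, let institution also interact with visit, since a term for level alone does not absorb site differences in change.
2. Define institution as the one known at randomisation, and list the participating institutions so that the categories are clear. State before unblinding how a very small site would be pooled.
3. State whether blocks are formed within institution. If they are not, stratify only where the list can still be changed. The article reports the list as already compiled and used to prepare envelopes of study medication, so restratifying could mean a new list and repacked stock. With institution in the model, stratification adds almost no precision, so item 1 matters more.

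**Cost.** Up to 5 degrees of freedom out of 320, and about 0.4% in the standard error if institution explains only 1% of variance.

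**Not covered.** Therapist clustering in the exercise arms would need its own clustering or random-effect term. As an illustration, take six clusters of 160/6 = 26.7 women and an assumed intraclass correlation of 0.05. The design effect is 1 + 25.7 × 0.05 = 2.28, the SE is 11 × √(1/160 + 2.28/160) = 1.576, and power for the exercise effect falls from 93.8% to 77.9%. The number of therapists is not stated, so this is not a finding about the trial's actual power.

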### Passive follow-up

All the women included in the study will undergo a passive follow-up interview at day 30^th ^after delivery. This follow-up will be performed via phone or direct house visit in those cases where no phone number is available for contact.

### Physical measurements

Anthropometric parameters will be determined in each participant at enrolment and before delivery. All measurements will be performed in fasting patients, wearing light clothes and without shoes, using standardized formats and methods. In addition, these parameters will be taken in duplicate by the same examiner on each woman.

Weight will be measured with the patient in standing position and then registered with 200 g approximation. The weight scale will be calibrated to 0 before each measurement.

Height will be measured using a metric tape with the patient in standing and vertical position leaned against the wall in Frankfort's position, and the value marked by a ruler placed horizontally on the head of the patient.

Heart rate or number of beats per minute will be measured in the radial artery.

Blood pressure will be taken twice (with a 5 min period between the measurements) using a mercury sphyngomanometer on the right arm, with the patient comfortably seated, after a 5 min rest. Systolic blood pressure (SBP) will be determined by the first audible sound (Korotkoff phase 1). Diastolic blood pressure (DBP) will be registered when the sound disappears (Korotkoff phase 5) [28]. The patient should not have smoked 30 min prior to the blood pressure measurement. The pneumatic arm cuff must cover 2/3 of the upper arm's length; its inferior border must be 2-3 cm over the antecubital space; the cuff will be slowly deflated. The mean blood pressure (MBP), will be calculated using the following formula [SBP+(2 × DBP)]/3.

Body composition that includes indirect fat mass percentage (FM; kg) and fat-free soft tissue mass (FFT; kg) will be measured at baseline and follow-up visits using indirect formulas [29].

Body Mass Index (BMI) will be estimated using the weight in kg divided by the second power of the height expressed in meters.

Functional Capacity (VO_2max_) will be determined in order to find the pregnancy-specific anaerobic threshold (AT). All women will perform an incremental sub-maxim exercise test of the ramp type. This test will be carried out on a mechanically braked cycloergometer (Monarck 820K) at a bench height to facilitate the most effective pedalling. Participants will be instructed to perform the test for as long as possible to ensure a true maximal attempt. Standard ACSM [19] test termination criteria will be monitored and followed throughout each test. After a 3-min warm-up at 20 watts, the work rate will increase every minute by 15 watts. Throughout the test, the pedalling rate will be set up at 60 rpm. Blood pressure, heart rate and perception of exhaustion will be monitored every minute. The incremental workload will be discontinued when either heart rate of 160 beat per min or the maximum level of exhaustion on Borg's scale are reached; another 3-min workload will be performed at 10 watts followed for cooling down before completion of the exercise test.

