### Inclusion Criteria

Nulliparous women not involved in a structured exercise program during pregnancy will be chosen, having a live fetus at the routine ultrasound scan, and a normal pregnancy, with gestational age 16 to 20 weeks. Written informed consent will be obtained from each woman prior to the inclusion in the study.

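### The cycle test is labelled sub-maximal and capped at 160 beats/min, yet women are told to make a maximal effort and the only other trial-specific stop is maximum Borg exhaustion

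*Protocol article*

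**What the plan says.** All of the conflicting text is in one paragraph of the protocol article, on functional capacity, under Physical measurements.

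- **Label:** "All women will perform an incremental sub-maxim exercise test of the ramp type".
- **Instruction to the woman:** "Participants will be instructed to perform the test for as long as possible to ensure a true maximal attempt".
- **Trial-specific stops:** the rising workload is "discontinued when either heart rate of 160 beat per min or the maximum level of exhaustion on Borg's scale are reached".
- **General stops:** "Standard ACSM [19] test termination criteria will be monitored and followed throughout each test". The criteria are cited but not listed.
- **Purpose:** the paragraph gives the aim as locating the anaerobic threshold specific to pregnancy. It has blood pressure, heart rate and perceived exertion checked each minute.

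The test belongs to Visit B. At Visit C, "within 32 and 36 week period of gestation, measurements described above are repeated" (Baseline assessments and active follow-up). On who takes it, Inclusion Criteria says: "Nulliparous women not involved in a structured exercise program during pregnancy will be chosen". The supervised training in the exercise arms is set at "moderate intensity (60-70% of maximal heart rate) measured by the 6-20 Borg's rating scale" (section 2, Exercise Group).

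**The concern.** A sub-maximal test is meant to stop short of a woman's limit, whereas a maximal attempt is meant to reach it. The paragraph asks for both. One member of staff could follow the label and let the woman ride quietly to the cap. Another could follow the instruction and urge her on for as long as she can last. Both would be following the written procedure.

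The women concerned are pregnant, were chosen because they are not in a structured exercise program, and repeat the test at 32 to 36 weeks. What is at stake is how hard they are asked to work, what they are told beforehand about the test, and whether sites conduct it in the same way. The main trial results are not at stake.

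**Working it through.** The plan states no figure to reproduce here. The check compares the written elements and adds one side calculation on the heart-rate cap.

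**Step 1. Sort the elements of the paragraph.**

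| Element | Character |
|---|---|
| Label | sub-maximal |
| Instruction to the woman | maximal |
| Heart-rate stop, 160 beats/min | sub-maximal for a typical woman (step 2) |
| Borg stop, highest level of exhaustion | maximal |
| ACSM termination criteria | cannot be classified, because they are not listed |

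The two trial-specific stops are joined by either/or, so the first one reached ends the increase in load. That rule is clear in itself. It does not fit the label for every woman, and the instruction does not fit the label for any woman.

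**Step 2. How far below maximum is 160 beats/min?**

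Inputs: ages 16 to 30 (Eligibility) and the cap of 160 (Physical measurements). The document gives no formula for maximal heart rate, so two common ones are assumed: 220 − age, and 208 − 0.7 × age.

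| Age | 220 − age | 160 as share | 208 − 0.7 × age | 160 as share |
|---|---|---|---|---|
| 16 | 204 | 160/204 = 78.4% | 196.8 | 160/196.8 = 81.3% |
| 20 | 200 | 160/200 = 80.0% | 194.0 | 160/194.0 = 82.5% |
| 25 | 195 | 160/195 = 82.1% | 190.5 | 160/190.5 = 84.0% |
| 30 | 190 | 160/190 = 84.2% | 187.0 | 160/187.0 = 85.6% |

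The cap therefore lies at about 78% to 86% of predicted maximum. A woman who reaches it has done a sub-maximal test, whatever she was told, and the instruction to give a true maximum was wrong for her.

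**Step 3. What happens to a woman who does not reach 160?**

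Predicted maxima are averages. If a woman's own maximum were 170, the cap would be 160/170 = 94.1% of it. If it were 160, the cap would be 100%. If it were 150, the cap would be 160/150 = 106.7% and could never operate. Early leg fatigue could also stop her from reaching 160. The only trial-specific limit left to such a woman is the top of the Borg scale. That is a score of 20 if the test uses the 6-20 scale that section 2, Exercise Group, names for training, which is an assumption. Otherwise only an ACSM criterion would end her test.

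**Step 4. Does any result depend on this?**

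Outcome variables lists flow-mediated dilatation and cord-blood F2-isoprostanes. Analytic plan names neither functional capacity nor VO2max, as an outcome or as a covariate. Section 2, Exercise Group, does not say that the test sets training intensity. No planned analysis uses the result.

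**The case against.** The strongest reply is that the paragraph works in practice. Three limits apply (160 beats/min, the Borg limit and the ACSM criteria) and the first one reached ends the test. Effort for as long as possible can be read as effort within those limits, and the Borg maximum as a backstop for a woman who cannot go on, not as a target. The women are also well screened. Exclusion criteria removes cardiovascular disease, bleeding, placenta praevia and conditions flagged by ACSM or ACOG guidance. Inclusion Criteria requires a normal pregnancy. Visit A includes an examination by a nurse and a gynecologist, Visit B includes an electrocardiogram, and the test is monitored every minute. An operations manual exists and may settle the conduct of the test.

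Much of this stands, and it keeps the point small. It does not remove the conflict. No reading of the limits accounts for telling women to make a true maximal attempt in a test called sub-maximal. The manual is not shown, but the article is not merely silent here: it states a procedure that contradicts itself.

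Three stronger readings are tempting, and the document supports none of them.

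- A reader might infer that every woman below 160 beats/min is taken to exhaustion. The ACSM criteria apply throughout and may stop her sooner.
- A reader might infer that the test is unsafe. The document does not show that harm would occur. The contrast with moderate training adds little, because a single capacity test and repeated training sessions serve different purposes.
- A reader might want a count of the tests affected. The share reaching the Borg maximum before 160 beats/min is not given and could be close to zero, so any count would be a guess.

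**Conclusion.** The point holds as a minor inconsistency in a stated procedure. The label and the heart-rate cap describe a sub-maximal test, while the instruction and the Borg stop describe a maximal one. A woman who stays below 160 beats/min may be urged on to maximum exhaustion unless an ACSM criterion intervenes.

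The contradiction rests on the wording alone. Placing the cap at about 78% to 86% of maximum rests on the two assumed age formulas, and reading the Borg stop as 20 rests on the 6-20 scale being the one used. The frequency is unknown. A reader might suppose that the trial's findings are weakened, but neither outcome nor any planned analysis uses the test. Confidence is medium, because the cited criteria and the operations manual cannot be seen.

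**What to change.** Keep the sub-maximal label, the 160 beats/min stop and the ACSM criteria, and make three changes to the functional capacity paragraph.

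1. Replace the sentence asking for a maximal attempt with: *Women pedal until the first stopping criterion is met (heart rate of 160 beats/min, the Borg limit or an ACSM criterion) or until they ask to stop.*
2. To match the label, replace the Borg maximum with a stated score below it. The investigators should choose the score so that the anaerobic threshold, the stated purpose of the test, can still be found. The document gives no basis for a particular value.
3. Call any VO2max derived from these data an estimated VO2max.

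The cost is a few sentences in the protocol and the matching line in the operations manual, settled before staff are trained. Heart rate and perceived exertion are already recorded every minute, so no visit, staff member, participant or data item is added. The downside is that some tests will end earlier, including tests of women who reach the new Borg limit before 160 beats/min but would have reached 160 before the Borg maximum. This is why the limit must be checked against the threshold before it is fixed. Replacing the instruction alone removes the main conflict in wording. The lower Borg limit brings the stopping rule into line with the label.
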